### Blinding

Due to the nature of the intervention and the choice of study design, the staff and research teams could not be blinded to the Unit’s training status.

### Statistical analysis

#### Pre-intervention period investigation

The secular background trend before the initiation of the study of the rate of term Low Apgar at 5 min will be described from the ISD SMR data using births between 2000 and the beginning of step 0.

#### Participation, loss to follow-up and withdrawal

Analysis and presentation of data will be in accordance with CONSORT guidelines and recommendations for Stepped Wedge available at the time of reporting [24]. Unit recruitment, in-house trainers’ participation to T3 training, and in-house PROMPT course implementation will be documented. Loss to follow-up will only occur in the unlikely event of a Maternity Unit closure.

Units that withdraw, or do not comply with the intervention, will be analysed on an intention-to-treat basis. If a Unit does not attend their allocated train the trainer session during the THISTLE study intervention or follow-up period, that Unit data will be excluded from the primary analysis (See section on sensitivity analysis). We do not anticipate extensive missing data for the primary outcome and our analysis strategy will be on complete cases. However, it is known that for a very small number of births, the Apgar score is not collected. We will describe any missing data in detail, and if required, will test the robustness of our primary analysis using appropriate imputation strategies [35].

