#### Inclusion criteria

The study population consists of the 15 Scottish Maternity Units with >900 births per year. Participating Units that have not previously undertaken PROMPT training (*n* = 12) have been randomised and will be part of the main analysis.

The three Units that have already undertaken PROMPT training will not be randomised but will be included in complementary analyses. Their inclusion will allow us to assess the intervention effect at a national scale, whilst giving us insight into the long-term sustainability of the intervention effect. The primary outcome will be derived for each of the 15 Maternity Units.

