All demographic, clinical and outcome data will be extracted from the ISD SMR 02 [29]. The ISD of the National Health Service, Scotland, is a national organisation for health information, statistics, and computing services and has been in existence for over 40 years. Anonymised patient based data for maternity care are routinely collected from the whole of Scotland and this database (specifically SMR02) will allow us to identify eligible births. The database is subjected to regular quality assurance checks and has been more than 99% complete since the late 1970s. Information from the Scottish Birth Record, another data source maintained by the ISD recording every baby born in Scotland but less exhaustive than the SMR 02, will also be used to complete information relative to the Apgar score missing in the SMR 02 [30].Data will be accessed remotely using the National Services Scotland Safe Haven, a secured facility allowing authorised researchers to analyse individual-level data while maintaining the utmost confidentiality. Permission to use the data has been approved by ISD (XRB13180). These data will be saved on the Safe Haven, only accessed by approved member of the research team (EL) and will be archived as per ISD regulations.

Maternal/infant characteristics will be limited to the date of birth and the Apgar score at 5 min. Preliminary research conducted by the co-applicants on term births in one Bristol local hospital have revealed the limited interest of risk adjusting the analysis of Low Apgar status at 5 min for maternal socio-demographics characteristics. To select the relevant population of term infants (see exclusion criteria), the following factors will be considered: type of birth (vaginal, emergency or elective CS); duration of gestation (<37, ≥37 weeks); place of birth (at home, transfer from a non-NHS Unit, transfer from a NHS Unit, in the Unit of interest); and intra-uterine deaths. We will extract the information from 2000 to the end of step 5. There are no patient-reported or economic outcomes.

Perinatal outcome data from the ISD SMR 02 will continue to be collected from participating Units irrespective of whether the PROMPT T3 training programme is undertaken and local PROMPT courses are implemented within the time span of the study.

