#### Main analysis

The number of births (count) and primary outcome will be tabulated by step (0 to 5) and by Unit. The primary outcome will be plotted for each Unit as well as globally for all Units to explore patterns visually. The primary outcome will be modelled at the level of the individual birth and analysed with a mixed (Generalized linear Mixed models strategies) or marginal (Generalized Estimating Equations) logistic regression model [36, 37] depending on encountered convergence or computational issues. This will allow us to account for the correlations between births occurring in the same Maternity Units. Initial models will assess the intervention effect (control period/step vs. intervention effect/step considering follow-up steps as intervention steps) and be adjusted for the effect of time-period to account for potential confounding effect of time, i.e. an underlying time-trend in the prevalence rate of Apgar score < 7 during the study period [38]. We will model the time-period using dummy indicators for each step. The interaction between time and the main intervention effect will then be tested to investigate the timing and duration of the intervention effect. All clusters will be analysed as randomised, i.e. we will make no allowance in these analyses for any Units that did not implement the intervention as per randomisation schedule. No interim analysis is planned, one final set of analyses will be conducted after the end of step 5, and as soon as the data are available.

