#### Additional analyses

To provide an assessment of the intervention effect across the health service, the 15 main Scottish Maternity Units will be considered in the next set of analyses. This will include the three Units trained prior to the start of the THISTLE study and the 12 Units targeted by this study, including those that have not implemented any local PROMPT courses.

Data from the three Units previously trained will be considered as part of the intervention periods throughout the analyses. Those Units not implementing any training will be considered as part of the control periods throughout the analyses. The data of the other Maternity Units will be considered as either part of the control or interventions periods depending on the date of implementation of their first local PROMPT course.

Finally, to provide an exhaustive understanding of those results, the 6-monthly rates of Low Apgar scores, scaled on a similar timing as the steps defined in Fig. 1, will be derived. They will be plotted for each of the 15 Units. These graphics will help to:understand any interactions between time and intervention effect as discussed aboveexplore the impact of the heterogeneity in the intervention implementation (timing and frequency of training sessions).

We will use an a priori assumption that the background rates of 5-min Apgar <7 among the 3 Maternity Units already trained will be lower than the other Units; and the Units which have not implemented any training are expected to have higher rates.

This graphic and two sets of sensitivity analyses will be used to discuss the relevance of the main analysis (and its extension) and determine the external validity of its findings, i.e. to what extent the findings can be generalised across the health service.

Studied centres have been followed until the 30th of September 2016 and related data will be accessible in March 2017.

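### The plan excludes a Unit that never attends T3 from the primary analysis, against its own intention-to-treat and as-randomised rules

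*Protocol article*

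**What the plan says.** Five places in the protocol article bear on a Unit that does not take up the programme.

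- **Participation, loss to follow-up and withdrawal**, general rule: "Units that withdraw, or do not comply with the intervention, will be analysed on an intention-to-treat basis".
- **Same paragraph, next sentence**: "If a Unit does not attend their allocated train the trainer session during the THISTLE study intervention or follow-up period", then "that Unit data will be excluded from the primary analysis". It points the reader to the sensitivity analyses.
- **Main analysis**: "All clusters will be analysed as randomised, i.e. we will make no allowance in these analyses for any Units that did not implement the intervention" according to the randomisation schedule.
- **Inclusion criteria**: the 12 Units not previously trained "have been randomised and will be part of the main analysis".
- **Data collection**: perinatal outcome data "will continue to be collected from participating Units irrespective of whether the PROMPT T3 training programme is undertaken".

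The Intervention section defines the intervention as the two-day T3 programme. The Randomisation section lets a Unit that cannot make its date move to another step, swapped with a Unit of similar size where possible. The Sensitivity analyses section already contains a per-protocol analysis limited to Units that have run at least one training session.

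**The concern.** T3 is the intervention, so a Unit that never attends is the most complete form of non-compliance. The general rule keeps such a Unit in and the next sentence takes it out. An analyst cannot follow both.

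The exclusion depends on what a Unit does after allocation, in a trial where Units and researchers know the allocation. The plan itself expects this behaviour to go with the outcome: the Additional analyses section assumes in advance that Units without any training will have higher low-Apgar rates. Removing them moves the primary estimate towards the effect among Units that took the programme up. The null hypothesis concerns PROMPT implemented at scale, and the Intervention section says implementation is to be assessed pragmatically. Failure to take the programme up is part of that question. With four Units per step, losing one also disturbs the size balance that the allocation method was chosen to secure.

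**Working it through.** **1. The rules applied to one Unit that never attends T3**

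| Section | Status in the primary analysis |
|---|---|
| Withdrawal paragraph, general rule | In, by intention to treat |
| Withdrawal paragraph, next sentence | Out |
| Main analysis | In, as randomised |
| Inclusion criteria | In, as one of the 12 |
| Data collection | Outcome data available |

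Four places point to inclusion, or at least make it possible, and one sentence excludes. Missing data do not force the exclusion. The point rests on this comparison and on no figure; the calculation below only gives scale.

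**2. Reproducing the planned power**

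Inputs from the Sample size section: *I* = 12 Units, four starting at each of steps 1 to 3; *T* = 6 periods (steps 0 to 5); *m* = 1200 births per Unit-period; ICC 0.1; rates 1.18% and 0.77%, a difference of 0.0041; alpha 5%. The section does not state sidedness, so two-sided is assumed. The variance is taken at the control rate, also an assumption.

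- Total variance: 0.0118 × 0.9882 = 0.011661
- Between-Unit: τ² = 0.1 × 0.011661 = 0.0011661
- Unit-period mean: σ² = 0.9 × 0.011661 / 1200 = 0.000008746

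Hussey-Hughes variance of the effect:

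Var = *I*σ²(σ² + *T*τ²) / [(*IU* − *W*)σ² + (*U*² + *ITU* − *TW* − *IV*)τ²]

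- *U* (treated Unit-periods) = 4 × (5 + 4 + 3) = 48
- *W* (squared period totals) = 0 + 16 + 64 + 144 + 144 + 144 = 512
- *V* (squared Unit totals) = 4 × (25 + 16 + 9) = 200
- *IU* − *W* = 576 − 512 = 64
- *U*² + *ITU* − *TW* − *IV* = 2304 + 3456 − 3072 − 2400 = 288

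Var = 12 × 0.000008746 × 0.0070052 / (64 × 0.000008746 + 288 × 0.0011661) = 0.000002185, so SE = 0.001478. Then 0.0041 / 0.001478 = 2.773, and Φ(2.773 − 1.960) = **79.2%**. The plan's 80% is reproduced.

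**3. One Unit excluded** (*I* = 11)

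- From step 1: *U* = 43, *W* = 421, *V* = 175. The two bracket terms are 52 and 236, giving **74.6%**.
- From step 2: *U* = 44, *W* = 428, *V* = 184. The terms are 56 and 248, giving **76.7%**.
- From step 3: *U* = 45, *W* = 443, *V* = 191. The terms are again 52 and 236, giving **74.6%**.

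**4. One never-trained Unit kept at its allocated step**

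The SE stays at 0.001478 but the expected effect shrinks. At this ICC and cluster size the model is almost a two-way comparison within Units and periods. The share of the effect lost is then the sum, over that Unit's allocated intervention periods, of the treatment indicator less its Unit mean and period mean plus the overall mean (48/72 = 2/3), divided by 288/72 = 4. The period means are 0, 1/3, 2/3, 1, 1, 1.

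| Allocated step | Share lost | Effect kept | Power |
|---|---|---|---|
| 1 | (25/6 − 4) / 4 = 0.042 | 96% | 75.7% |
| 2 | (4 − 11/3) / 4 = 0.083 | 92% | 72.0% |
| 3 | (7/2 − 3) / 4 = 0.125 | 88% | 68.0% |

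Power is Φ(share kept × 2.773 − 1.960). A direct calculation with the full mixed-model weights gives 95.8%, 91.7% and 87.5% of the effect.

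**5. Comparison**

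Excluding one Unit costs 79.2 − 76.7 = 2.5 to 79.2 − 74.6 = 4.6 points. Keeping it costs 3.5, 7.2 or 11.2 points. With the variance taken at the mean of the two rates, the full design has 86.2%, exclusion gives 82.2% to 84.0%, and keeping gives 83.2%, 79.8% or 76.0%. The ordering is the same.

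**The case against.** The strongest defence reads the withdrawal paragraph as a general rule with one exception fixed in advance. Units that took T3 but trained late or not at all stay in; only a Unit that never started is left out. The Main analysis sentence about not implementing to schedule would then concern the first group. A reader might infer that the rule was left open so that the population could be chosen after seeing results. The documents do not show that, and this reading argues against it. It does not remove the conflict, however: the Main analysis section speaks of all clusters, and the general rule covers non-compliance without qualification.

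A reader might also infer that any Unit missing its date is dropped. That is not supported. The exclusion sentence refers to the study's intervention or follow-up period, and the Randomisation section answers staff shortage at the allocated date with reassignment. The clause affects only never-attenders. There may be none: the abstract says teams from each participating Unit attended T3. This limits the scope but does not justify the wording.

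Nor does power argue for keeping the Unit. For a step 2 or step 3 Unit, keeping it costs more power than excluding it. This objection stands in full.

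Finally, the size of any selection bias is not shown. A constant difference in level between Units is largely absorbed by the Unit effect; a different time course is not. Under Additional analyses, non-implementing Units do return in the 15-Unit analysis, but as controls: "Those Units not implementing any training will be considered as part of the control periods throughout the analyses". That is not the as-randomised comparison.

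**Conclusion.** The contradiction holds and must be resolved, because it decides who is in the primary analysis of a 12-cluster trial. It is confined to Units that never attend T3 during the study.

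For one such Unit the two rules target effects that differ by about 4% to 12%, assuming the full effect in every other Unit and none in that one. The lower figure is part of the at-scale effect that the trial sets out to measure. The power figures assume equal Unit sizes, a normal approximation, two-sided 5% and one non-attending Unit, a number the documents do not give. They show scale only. The argument is that the primary analysis should not select clusters on behaviour after allocation when their outcomes are available. A claim that the planned exclusion has biased the result by a known amount would go beyond the documents.

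**What to change.** Delete the exclusion sentence from the section on participation, loss to follow-up and withdrawal. State there and under Main analysis that all 12 Units enter the primary analysis at their allocated step, whether or not the team attended T3. Confine exclusion to the per-protocol analysis under Sensitivity analyses, which is already limited to Units that have run at least one session.

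The Trial status section says analyses are under way, so the report should also state how many Units the clause would have affected, even if none.

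The cost is one sentence and no new data. The downside is dilution if a Unit never trained: about 4%, 8% or 12% of the effect for a step 1, 2 or 3 Unit, and more power lost than by exclusion for steps 2 and 3. This should be acknowledged openly, with the per-protocol result reported alongside.

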#### Baseline characteristics and intervention delivery (process measures)

Appropriate descriptive statistics will be used to summarise all baseline characteristics. The number of staff (total and by professional group), number of PROMPT courses delivered by in-house trainers and the length of time required to train all the staff will also be reported for each of the 12 Units.

#### Main analysis

The number of births (count) and primary outcome will be tabulated by step (0 to 5) and by Unit. The primary outcome will be plotted for each Unit as well as globally for all Units to explore patterns visually. The primary outcome will be modelled at the level of the individual birth and analysed with a mixed (Generalized linear Mixed models strategies) or marginal (Generalized Estimating Equations) logistic regression model [36, 37] depending on encountered convergence or computational issues. This will allow us to account for the correlations between births occurring in the same Maternity Units. Initial models will assess the intervention effect (control period/step vs. intervention effect/step considering follow-up steps as intervention steps) and be adjusted for the effect of time-period to account for potential confounding effect of time, i.e. an underlying time-trend in the prevalence rate of Apgar score < 7 during the study period [38]. We will model the time-period using dummy indicators for each step. The interaction between time and the main intervention effect will then be tested to investigate the timing and duration of the intervention effect. All clusters will be analysed as randomised, i.e. we will make no allowance in these analyses for any Units that did not implement the intervention as per randomisation schedule. No interim analysis is planned, one final set of analyses will be conducted after the end of step 5, and as soon as the data are available.

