### Sample size

Of a total of fifteen Maternity Units with >900 births per year in Scotland (in 2010) three Units have already undertaken the PROMPT Train the Trainers day and had started implementing the intervention prior to the start of this study. These three Units are excluded in the following power calculation which focuses on the remaining eligible 12 Units that will contribute data to the before and after intervention periods. Annual birth numbers per Unit are available via an anonymised aggregated Maternity Unit dataset from SMDR for the period 2004–2010. We have made a conservative assumption that the Maternity Units which have already undergone PROMPT training are the three largest Units in the anonymised data. The 12 remaining Units had an Apgar < 7 rate at term of 1.18% in 2010 and an average monthly 200 births per Maternity Unit, i.e. around 1200 births per semester (duration of a step).

Using the method to calculate power for Stepped Wedge designs defined by Hussey and Hughes [25] and its Stata implementation [31], and considering that all available and eligible data for the considered Maternity Units will be analysed, the following intervention effectiveness can be detected: With a power of 80% (alpha = 5%), four Maternity Units randomised at each step with three intervention steps - steps 1 to 3 - (12 Units(clusters) in total) and two follow-up steps - steps 4 and 5 -, of six-month duration each (steps 1 to 5), an average cluster size of 1200 births, and an intra-cluster correlation coefficient of 0.1, we will be able to detect a reduction of 35% or more in the Apgar < 7 rate (i.e. 1.18% vs 0.77%).

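### The single primary test is left open between a mixed and a GEE logistic model, chosen by convergence, on 12 Units with no small-sample method stated

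*Protocol article*

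**What the plan says.** Under Main analysis, the protocol article models individual births with a "mixed (Generalized linear Mixed models strategies) or marginal (Generalized Estimating Equations) logistic regression model [36, 37] depending on encountered convergence or computational issues". Of clustering it says: "This will allow us to account for the correlations between births occurring in the same Maternity Units". Time enters as one indicator per step. The article does not state a working correlation, a type of standard error, a reference distribution, a small-sample correction or a Unit-by-step effect. It does not rule any of these out either.

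Under Sample size, the trial has "12 Units(clusters) in total", a 5% alpha and 80% power for a 35% reduction. There is one primary outcome and no secondary outcome. Under Trial status, the final extract is already accessible and analyses are under way.

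**The concern.** The article states a rule for choosing the primary estimator, and that rule depends on how the models behave once fitted to the outcome data. It sets no criterion for non-convergence and fixes no form for either route.

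With 12 clusters the two routes do not give interchangeable tests, and they fail for different reasons:

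- **GEE.** The sandwich variance is built from 12 independent Unit contributions and is biased low when there are so few.
- **Mixed model.** A Unit random intercept alone treats each Unit's departure from the common time trend as constant. If Unit rates drift from step to step, the standard error is too small.

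In either case a nominal p < 0.05 would be a false positive more often than claimed, and the confidence interval would be too narrow, on the only result that carries the trial's conclusion.

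**Working it through.** **Inputs from the document.** Alpha 5% (sidedness not stated; two-sided assumed). I = 12 Units, with "four Maternity Units randomised at each step with three intervention steps". T = 6 periods, since results "will be tabulated by step (0 to 5) and by Unit". "an average cluster size of 1200 births, and an intra-cluster correlation coefficient of 0.1". Control rate: "Apgar < 7 rate at term of 1.18% in 2010". Target rate 0.77%.

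**1. Reproduce the plan's power (Hussey and Hughes).** Units are treated for 5, 4 or 3 periods, so:

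- U = 4(5 + 4 + 3) = 48
- W = 4² + 8² + 3 × 12² = 512
- V = 4(25 + 16 + 9) = 200

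Total variance is 0.0118 × 0.9882 = 0.011661. With ICC 0.1, τ² = 0.0011661 and σ² = 0.9 × 0.011661 / 1200 = 8.746 × 10⁻⁶.

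Var = Iσ²(σ² + Tτ²) / [(IU − W)σ² + (U² + ITU − TW − IV)τ²]

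Here IU − W = 64 and the second bracket is 2304 + 3456 − 3072 − 2400 = 288. This gives Var = 2.185 × 10⁻⁶ and SE = 0.001478.

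Power = Φ(0.0041/0.001478 − 1.96) = Φ(0.813) = 79.2%. The detectable reduction is 2.80 × 0.001478 / 0.0118 = 35.1%. The stated figure reproduces. It does so with a z reference and a constant Unit effect, that is, no Unit-by-step variation and no small-sample allowance.

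**2. Type I error by simulation under no effect.** There were 2,000 trials per scenario, with Monte Carlo SE near 10% of √(0.1 × 0.9/2000) = 0.7 points. Each trial had 12 Units, 6 steps and rate 1.18%, with 1200 births per Unit-step or sizes from 500 to 2300. Assumed SDs on the log-odds scale were 0.2 or 0.3 between Units, and 0, 0.1, 0.2 or 0.3 for Unit-by-step. All models included step indicators.

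| Analysis | Type I error at nominal 5% |
|---|---|
| Exchangeable GEE, uncorrected sandwich, z | 10.2-12.4% |
| Independence GEE, uncorrected sandwich, z | 11.6-13.3% |
| Either GEE, uncorrected sandwich, t(10) | 7.0-9.8% |
| Either GEE, Kauermann-Carroll, t(10) | 4.6-7.2% |
| Either GEE, Mancl-DeRouen, t(10) | 3.2-4.8% |
| Random-intercept mixed model, z, Unit-by-step SD 0 | 5.0-6.0% |
| same, SD 0.1 | about 7% |
| same, SD 0.2 | about 12.5% |
| same, SD 0.3 | about 22% |

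The sandwich GEE rates barely change as the Unit-by-step SD goes from 0 to 0.3, so the cause there is the number of clusters. In the mixed model the cause is the omitted Unit-by-step term. A t reference alone does not cure that: with unequal sizes and Unit SD 0.3, the random-intercept model with t(10) gave 4.2%, 7.8% and 16.3% at Unit-by-step SD 0.1, 0.2 and 0.3.

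**3. What a drift SD of 0.2 means.** For a rare outcome, odds are close to rates. One SD either way is a factor of e^0.2 = 1.22, so 1.18% becomes about 1.44% or 0.97%. A Unit-step expects 1200 × 0.0118 = 14.2 events, so sampling noise on the log scale is about 1/√14.2 = 0.27. Drift of 0.2 would therefore be hard to see in the planned plots.

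**4. Cost of the t reference.** The critical value goes from 1.960 to 2.228, a ratio of 1.137, so intervals are about 14% wider. With noncentrality 1.960 + 0.842 = 2.80, the noncentral t on 10 df gives power of about 71% where z gives 80%.

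**The case against.** The strongest reply is that the article is condensed and its SAP is not shown. Standard-error type, reference distribution and random-effect structure commonly sit in a SAP, so silence here is not evidence that no correction is planned. That stands. A reader might infer that the trial's test has an inflated error rate; the document supports only the statement that it would have one if the uncorrected forms were used.

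The sentence on correlation within Units also does not exclude a Unit-by-step effect, because births in the same Unit and step are births in the same Unit. That stands too.

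Two further inferences go too far:

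- **That neither route holds 5%.** The random-intercept mixed model stays at 5-7% when the Unit-by-step SD is 0 to 0.1.
- **That GEE error reaches about 20%.** The sandwich z test gave 10-13% in the scenarios above. In a separate set of 1,000-trial scenarios with Unit-size CV up to 0.6, exchangeable stayed at 11.2-12.2% while independence reached 16.7%. The document names no working correlation.

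Finally, the choice is tied to computation and not to the estimate or p-value, the mixed model is named first, and how often it would fail to converge is unknown. This lowers the practical risk. It does not supply a criterion for failure or fix the form of either model.

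**Conclusion.** The point holds in conditional form. The article fixes the choice of primary estimator badly: two models, picked by convergence, with no criterion and no stated small-sample method on 12 Units. If the GEE route is run as an uncorrected sandwich z test, type I error is about 10-13%, roughly two to 2.7 times the stated 5%. If the mixed route has only a Unit intercept, error is about 5-7% with little drift, about 12% at a Unit-by-step SD of 0.2 and about 22% at 0.3.

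These figures rest on a two-sided test, on assumed Unit SDs of 0.2-0.3 and Unit-by-step SDs of 0-0.3, and on no correction being applied. The GEE figure is insensitive to the drift assumption; the mixed-model figure depends on it entirely. Because an unseen SAP may already settle the matter, this should be clarified and fixed before the result is read, but it is not a fatal flaw in the plan.

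**What to change.** Before the primary result is read, replace the open choice with a fixed order:

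1. **Primary model.** Logistic mixed model with step indicators, random effects for Unit and Unit-by-step, and small-sample t inference with the degrees of freedom stated.
2. **Trigger.** Define non-convergence in advance (software, estimation method, tolerance, permitted restarts). Say that a Unit-by-step variance estimated at zero is not in itself a failure.
3. **Fallback.** Exchangeable GEE with a small-sample-corrected variance, such as Kauermann-Carroll, and t on about 10 df. Mancl-DeRouen performs comparably and is slightly conservative with t(10). Report which route was used and why.

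The simulations above cover the fallback, at about 5-7%. They do not cover the recommended mixed model, whose error rate should be checked by simulation when its degrees of freedom are set.

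A permutation test is optional. It is valid only if the realised allocation lies in the randomisation set. The Randomisation section lets Units be swapped between steps for local reasons and constrains one Unit to step 1, so this must be confirmed first.

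The work is SAP wording and standard software options. The statistical cost is not trivial: intervals about 14% wider from the t reference alone, and power of about 71% in place of 80%. Power should be restated on that basis, and any real Unit-by-step variation would lower it further.

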Details of the study design are presented in Fig. 1. The study has one control period (step 0) during which none of the Units receives training, three intervention (steps 1–3) and two follow-up (step 5) periods, each lasting 6 months. This duration allows all 12 Units to receive their training (see section on intervention) within 12 months, keeping each step short to reduce contamination between trained and untrained Units (rotation of trained staff between Units) but also to remain within the funding and time constraints while allowing for follow-up periods. Based on previous experience [16, 26] it was anticipated that Units would be able to train all of their staff within one year of commencing their local training. Four Maternity Units are randomised to each intervention step, i.e. the intervention is rolled-out sequentially to the Units in groups of four.

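### The planned time-by-intervention interaction is estimable only as a step 2 versus step 1 contrast, so it cannot show the timing or duration of the effect

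*Protocol article*

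**What the plan says.** The roll-out is set out under Study design and Sample size in the protocol article. "The study has one control period (step 0) during which none of the Units receives training". Then "Four Maternity Units are randomised to each intervention step", namely steps 1, 2 and 3, followed by "two follow-up steps - steps 4 and 5 -, of six-month duration each (steps 1 to 5)".

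Under Main analysis, exposure is binary, "considering follow-up steps as intervention steps", and Units are analysed by allocated step. Calendar time is a confounder to be adjusted for: "We will model the time-period using dummy indicators for each step". The next sentence adds the interaction and gives its purpose: "The interaction between time and the main intervention effect will then be tested to investigate the timing and duration of the intervention effect".

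Under Additional analyses, plots of six-monthly rates are meant to help "understand any interactions between time and intervention effect as discussed" earlier, so they refer back to the same interaction. The article defines no model term for time since a Unit crossed over.

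**The concern.** An intervention effect at a given calendar step can be estimated only if that step contains both trained and untrained Units. Here every Unit is on the intervention from step 3 onwards. A model with a dummy for each step therefore cannot separate the intervention effect in steps 3, 4 or 5 from the calendar effect of those steps.

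This matters because the protocol cares about both build-up and persistence. Under Study design and Intervention, Units are expected to need about a year to train all staff, so an effect should grow over at least two semesters. The Intervention section names sustainability as something the trial is to determine, and two follow-up steps were included. If the only inferential test of timing and duration cannot use those steps, its result, significant or not, will not answer the question it was planned for.

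**Working it through.** **Inputs.** 12 Units, with four crossing over at each of steps 1, 2 and 3, and six periods (steps 0 to 5) (Study design, Sample size). 1,200 births per Unit and step, ICC 0.1, rates 1.18% and 0.77%, alpha 5%, power 80% (Sample size). Two-sided alpha is assumed, because the article does not state sidedness.

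**The plan's own power figure.** The Hussey and Hughes variance with six periods, and total variance p(1−p) at p = 1.18% split by the ICC, gives 79.2% power for 1.18% versus 0.77%. The stated 80% is reproduced and is not in dispute.

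**Step 1: trained and untrained Units by step.**

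| Step | Intervention | Control |
|---|---|---|
| 0 | 0 | 12 |
| 1 | 4 | 8 |
| 2 | 8 | 4 |
| 3 | 12 | 0 |
| 4 | 12 | 0 |
| 5 | 12 | 0 |

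For steps 3, 4 and 5 the intervention-by-step column is identical to the step dummy. For step 0 it is all zeros.

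**Step 2: rank of the 72-row Unit-by-step design.**

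| Terms | Without Unit effects | With Unit effects |
|---|---|---|
| Step dummies | 6 | 17 |
| + intervention | 7 | 18 |
| + all intervention-by-step terms | 8 | 19 |
| Step dummies + five exposure-semester indicators | 11 | 22 |

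The interaction adds 8 − 7 = 1 (or 19 − 18 = 1) degree of freedom, against a nominal five. Making time linear in the interaction, with the step dummies kept, gives the same 8 and 19.

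**Step 3: what the single contrast is.** It is the effect at step 2 minus the effect at step 1. Step 1 starts on 1 April 2014 and steps last six months, so it compares October 2014 to March 2015 with April to September 2014. At step 2, four trained Units are in their second exposed semester and four in their first, so even this contrast does not isolate length of exposure.

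**Step 4: its precision.** Generalised least squares on the risk-difference scale, Cov = (Σ X′V⁻¹X)⁻¹, with V = (σ²/1200)I + τ²J for each Unit.
- σ² = (0.0118 × 0.9882 + 0.0077 × 0.9923)/2 = 0.00965, and τ² = σ² × ICC/(1 − ICC).
- SE of the contrast: 0.257 percentage points at ICC 0.1 and 0.255 at ICC 0.001.
- Planned effect: 1.18 − 0.77 = 0.41 points.
- Power if the effect is zero at step 1 and full size at step 2: Φ(0.41/0.2565 − 1.96) = Φ(−0.36) ≈ 36%.
- Difference detectable with 80% power: 2.80 × 0.2565 ≈ 0.72 points.

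**Step 5: the alternative coding.** With indicators for the 1st to 5th semester since the allocated start, and the step dummies kept, all five effects are estimable.

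| Quantity (percentage points) | Six periods | Plus four earlier semesters |
|---|---|---|
| SE of semester 1, 2, 3, 4, 5 effects (ICC 0.1) | 0.17, 0.25, 0.34, 0.43, 0.53 | 0.14, 0.18, 0.24, 0.28, 0.35 |
| SE of the average of the five (ICC 0.001 to 0.1) | 0.27 to 0.33 | 0.20 to 0.21 |
| SE of 5th minus 1st (ICC 0.001 to 0.1) | 0.36 to 0.43 | 0.29 to 0.30 |

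For comparison, the SE of the single constant effect with six periods at ICC 0.1 is 0.14.

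**The case against.** The strongest reply is that the sentence has been read too literally. Its stated purpose, timing and duration, suggests time since training began. Coding an interaction is normally SAP detail, and on that reading the effects are estimable. But the only time variable the article defines is the calendar step, in the sentence just before. The complaint is not that detail is missing: the coding and the purpose are both stated, and the one does not serve the other. If exposure time was meant, the remedy is the same: say so.

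Second, timing is also addressed elsewhere. Sensitivity analyses vary the step lengths and use actual start dates. The 15-Unit analysis adds Units trained throughout and any never trained, and the rates are plotted. These do give extra information, and timing does not hang on one test. But the later contrasts they create are not randomised, and none of them redefines the interaction.

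Third, the Standard care section has all Units leaving standard care at the start of step 4, which it calls the last intervention period, whereas Study design and Sample size place the intervention periods at steps 1 to 3. These passages must be reconciled. If the last group were coded as crossing at step 4, step 3 would become estimable too, but steps 4 and 5 would not.

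Fourth, the remedy has limited power. This stands. With six periods, a 5th-minus-1st difference needs about 1.0 to 1.2 points for 80% power, close to the whole 1.18% baseline rate, and only four Units reach a fifth semester. How readers would interpret a null result is also conjecture, and the point does not rest on it.

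**Conclusion.** The concern holds. For the 12 Units analysed as randomised with calendar-step dummies, the interaction reduces to one contrast between two adjacent steps in the first year of roll-out. It cannot inform on duration, and it has about 36% power in the favourable case above. The non-estimability is algebraic and depends on no assumption about rates or ICC. It depends only on time meaning calendar step and on cross-over at steps 1, 2 and 3. The standard errors assume a linear risk scale, equal Unit sizes, averaged binomial variance and a constant within-Unit correlation over time. With variance taken at the 1.18% rate, power falls to about 31%.

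The primary intervention effect and the stated power are not affected. This should be corrected, but it does not threaten the main result.

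**What to change.** Replace the calendar-step interaction with the intervention effect by semester since the allocated step start (1st to 5th), keeping the step dummies. Test equality of the five effects (4 degrees of freedom) and a linear trend across them. Report each semester's effect with its confidence interval, so that a non-significant test is not the only evidence on persistence. State the assumption that the effect depends on length of exposure and not on calendar date.

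Add pre-roll-out semesters as control periods. Data back to 2000 are already to be extracted, and four extra semesters lower the SE of the average effect from 0.27–0.33 to 0.20–0.21 points and that of the 5th-minus-1st difference from 0.36–0.43 to 0.29–0.30. This assumes that within-Unit correlation holds over the longer span. It does not make the persistence test strong: about 0.8 points would still be needed for 80% power.

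The cost is SAP wording and a refitted model. Later-semester intervals will be wide, and the report should say so. Because Trial status says the final data are accessible and analysis is under way, the change should be dated and declared as such.
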